#### Intervention

The web page will include the 9 sessions that comprise the CBT-based treatment (Table 1). The sessions will be weekly. Each week, the participant will find a brief summary of the previous session and an introduction to the topic being covered, with an explanation of the new session. The participant will then be provided with the new information (the subject matter) and various examples will be included to facilitate understanding. Once the information is introduced, a summary of the key ideas of the session will be presented and a short evaluation will assess the subject’s understanding. At the end of the session, the person will have the key ideas and a self-assessment of the session. Finally, the participant will receive an explanation of the task to be completed and forwarded to the therapist with an example of how the task should be carried out. The therapist will respond and provide feedback on the completed assignment, but no personal advice will be given. Each session will need to be completed in order to have the following session available. In addition, the participant will have a bibliography of each of the topics covered. Each session will last 20–30 minutes.

**Table 1 pone.0274551.t001:** Treatment sessions.

Session	Topic
1	What is depression? Relationship between cognitions, behavior and emotions. Relationship between diabetes and depression.
2	Relationship between stress and diabetes. Use of relaxation and physical exercise for the management of stress and diabetes.
3	Coping in diabetes. How to face the fears associated with diabetes (short-/medium- and long-term complications).
4	Identification, definition and resolution of problems. The demands of daily self-care.
5	Pleasurable activities. Incorporation of a physically and mentally healthy lifestyle plan.
6	Cognitive restructuring. Modification of beliefs and cognitive errors in diabetes.
7	Social skills: communication style. Working towards an assertive communication style. Communication with family, friends and medical professionals.
8	Importance of support. Searching for sources of support regarding diabetes.
9	Relapse prevention.

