Therapists will send e-mails to the TG participants to encourage them to continue their efforts and they will be called if there is no response to these e-mails. Halfway through the program, their opinions about it will be sought (doubts, suggestions for improvement). This is intended to motivate the participants in order to improve adherence and minimize the risk of drop out.

The CG (waiting list) participants will receive a telephone call or e-mail informing them of the next program start date. In the event that during the study an individual (CG or TG) is found to have a worsening depressive mood (severe depression or suicidal ideation), the participant would discontinue the study and his or her physician would be notified in order to refer the individual to the Clinical Management Unit of Mental Health of the Andalusian Health Service.

Protocol amendments: Important protocol modifications will be reported to the researchers, the University of Malaga and the protocol registry.

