### Statistical analysis

First, a descriptive analysis will be conducted of the variables studied. For quantitative variables, measures of centralization and dispersion will be collected. For qualitative variables, a frequency analysis will be carried out.

To analyze cross-sectional and longitudinal differences, hypotheses will be contrasted at a 95% confidence level. To contrast differences between both groups (TG and CG) at baseline and post-treatment at a given time, Student’s *t*-test will be used (for strong violations of the normality assumption, the Mann-Whitney U-test) or analysis of variance (ANOVA). The effect size will be calculated using Cohen’s d.

To test whether the treatment produces differences over time (baseline, post-treatment, 3 months, 6 months and 12 months in the TG and baseline and post-treatment in the CG) in each of the groups, the *t*-test for related samples will be used (Wilcoxon signed-rank test in the event of strong violations of the normality assumption) or with an ANOVA for repeated variables and multiple regression model to control possible confounding variables (such as: age, gender, HbA1c, time with diabetes, etc.). For qualitative variables, McNemar’s test will be used.

To study the relationships between the different variables, Pearson’s correlation coefficient and linear regression models will be used for interval variables. The relationship between qualitative variables will be evaluated with the χ2 test.

Possible risk factors will be studied through logistic regression analysis (analysis of adherence to the treatment program).

The analyses will be carried out considering the subjects who complete the program. Analyses will also be carried out according to the protocol.

Analysis of the results will begin when the TG subjects have completed all of the phases of the treatment program. An improvement in the different variables will be taken into account in the following cases: significant differences in p≤0.05 and in the case of the BDI-FS when there is a decrease in the level of depressive symptomatology (moderate-mild, mild-minimum).

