We start from a treatment that is recognized as effective in the population in which it is to be applied [29–34] in depressive symptoms or depression and distress related to diabetes. However, no significant results were found regarding glycemic control, understood as the glycosylated hemoglobin (HbA1c) value. A possible explanation could be that, despite working with aspects related to the impact on the patient’s mood, changes in the treatment regimens for diabetes care are not directly addressed. This would make sense, as it is not the aim of this type of intervention. The study of other outcome variables of the web treatment on glycemic control, such as number of self-tests, episodes of hypoglycemia and hyperglycemia, and treatment adherence could add information along these lines. Moreover, other outcome variables with implications for treatment adherence, such as specific diabetes-related distress or fear of hypoglycemia, may also indicate structural changes that could influence long-term glycemic control. In addition, the number of sessions involved in treatment in previous studies has varied between 6 [32–36], 7 [37, 38] and 8 [29–31] treatment sessions. Based on previous studies and the existing relationships between depression and other variables in people with type 1 diabetes, in this study we have created 9 sessions.

Although it is known that adherence to Internet-based CBT treatment is lower than adherence when delivering the same treatment face to face [59], in the population with diabetes, there appears to be no difference between the two types of delivery [28]. Determining the variables involved in adherence to treatment will be among the data to be obtained in the present study. Accordingly, a comprehensive analysis of the medical and psychological variables involved in depression in people with diabetes, together with the variables that may affect adherence to this type of treatment in our study population, may help to provide greater insight into the effects of this treatment and the characteristics of the population in which it would be most beneficial (adherence), which are the main strengths of this study.

However, this study is not without limitations. The sample sizes of the previous studies are larger than the figure we aim to achieve in this study. Nevertheless, taking into account the rigor of the exclusion criteria and the sample size calculations described previously will enable reliable and valid conclusions to be drawn.

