## Conclusions

In this article, we present the design and methodology of the WEB_TDDI1 study, which includes a specific proposal for the treatment of mild-moderate depressive symptoms in adults with type 1 diabetes delivered through a Web-based CBT program. Based on previous studies, we anticipate an improvement in depressive symptomatology with respect to the control group and to baseline status, as well as an improvement in the secondary variables studied related to depression (anxiety, diabetes-related distress, fear of hypoglycemia, coping strategies, quality of life and adherence to diabetes treatment). Thus, this program is expected to provide professionals with a tool to treat mild to moderate depressive symptomatology in people with type 1 diabetes. Additionally, an analysis of the characteristics related to adherence to this program will be carried out to help establish profiles of people who will benefit from this type of treatment.

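### The planned regression of programme adherence falls under a completers-only rule which, if adherence means finishing the programme, leaves it no non-adherent participants

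*Protocol article*

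**What the plan says.** The Statistical analysis section of the protocol article lists the methods and includes a model of programme adherence: "Possible risk factors will be studied through logistic regression analysis (analysis of adherence to the treatment program". The paragraph directly after it sets the population: "The analyses will be carried out considering the subjects who complete the program". One further sentence adds a second set: "Analyses will also be carried out according to the protocol". Neither set is defined further, no set of all starters or all randomised participants is named, and no analysis is exempted.

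The Intervention section describes the programme. On its length: "The web page will include the 9 sessions that comprise the CBT-based treatment (Table 1". On access: "Each session will need to be completed in order to have the following session available". The same section provides that a participant in either group whose mood worsens to severe depression or suicidal ideation leaves the trial: "the participant would discontinue the study and his or her physician would be notified".

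The adherence analysis is given weight elsewhere. The Discussion states: "Determining the variables involved in adherence to treatment will be among the data to be obtained in the present study". It then counts the study of variables affecting adherence among the main strengths. The Conclusions add that "an analysis of the characteristics related to adherence to this program will be carried out to help establish profiles of people" who stand to benefit.

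**The concern.** A model of who adheres needs both adherers and non-adherers. The stated population rule selects on finishing the programme, which is either the adherence outcome itself or something close to it. Applied as written, the rule removes the people whose characteristics the model is meant to explain: those who stop partway.

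At stake is a secondary aim that the article advertises. A model restricted to completers cannot say which patients are likely to drop out of web-based treatment, and profiles built on it would describe only differences among people who all finished.

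The same sentence also affects the randomised comparison of treatment and waiting list. That is a separate and more serious matter with its own remedy. Naming an intention-to-treat set for efficacy would not by itself define adherence or the population for the adherence model.

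**Working it through.** The document states no figure for this analysis, so there is none to reproduce. The check is one of set logic, followed by two short calculations.

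**Inputs**
- Outcome: adherence to the programme, binary because the method is logistic regression (Statistical analysis). No cut-off is given.
- Population: completers, plus a second undefined set (Statistical analysis).
- Programme: 9 sessions, each opening only after the one before is completed (Intervention).
- Treatment group: 28 participants; both groups: 56 (Sample size calculation).
- Completion rate: not stated. A range of 60% to 90% is assumed below.

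**Step 1: what a completer is.** Because sessions open in sequence, a participant cannot skip any and still reach session 9. A completer has therefore most naturally done 9 of 9 sessions. This is an inference; the article does not define completion.

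**Step 2: the outcome within the completer set.** If adherent means having completed the programme, every completer scores 1. Non-adherent participants in the set number 0 at any dropout rate.

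**Step 3: what the model does with a constant outcome.** With *n* participants all scoring 1 and intercept *b*, the log-likelihood is −*n* × ln(1 + e^(−*b*)). For an illustrative *n* = 20:

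| *b* | log-likelihood |
|---|---|
| 0 | −13.86 |
| 2 | −2.54 |
| 5 | −0.134 |
| 10 | −0.0009 |
| 20 | about 0 |

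It rises towards 0 without reaching a maximum. There is no finite estimate, and no covariate effect can be estimated.

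**Step 4: how many participants the rule leaves out.** Expected non-completers among the treated = 28 × (1 − completion rate):

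| Assumed completion | Calculation | Non-completers of 28 | Kept in completer set |
|---|---|---|---|
| 90% | 28 × 0.10 | 2.8 | 0 |
| 80% | 28 × 0.20 | 5.6 | 0 |
| 70% | 28 × 0.30 | 8.4 | 0 |
| 60% | 28 × 0.40 | 11.2 | 0 |

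The waiting-list group is offered the programme later if still eligible. If all 56 were eventually treated, the numbers would double, to between 5.6 and 22.4.

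**Step 5: other definitions of adherence.** The Intervention section also describes a weekly rhythm and a task sent to the therapist after each session. Adherence measured by timeliness or by tasks returned could vary among completers, so the model could then be fitted. The non-completers in Step 4 would still be absent.

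**The case against.** The strongest reply is that the completer sentence was meant for the outcome comparisons that fill most of the section. A model of adherence obviously needs non-adherers, and the Discussion speaks of adherence in the study population, not among completers. The article condenses a fuller protocol, where the population for an exploratory model would ordinarily be set. The authors may well have intended this. But the difficulty is not a missing detail: the article states a population rule, places it directly after the adherence model and makes no exception. A stated rule that conflicts with a stated analysis needs reconciling in the text.

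Four further points stand, and they limit the conclusion.
- A reader might infer that a trial endpoint cannot be scored. The document does not support that. Programme adherence is not in Table 2 or among the secondary variables. The treatment adherence listed there is diabetes self-care by the SCI-R questionnaire, which can be scored in completers.
- A reader might also infer that the model fails whatever is done. That holds only if adherence means completion and the set is completers. Both the 9-of-9 reading and the equation of adherence with completion are inferred.
- The second set is undefined. If it means per-protocol, it probably drops non-adherers too, but the text does not settle this, and some partial adherers might remain in it.
- The constant-outcome calculation shows what follows from that reading; it does not show that the trial will produce such data.

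**Conclusion.** The point holds in a conditional form. As written, the completer restriction covers the programme-adherence regression. If adherence means completing the nine sequential sessions, the analysed set contains 0 non-adherent participants and the model cannot be estimated. If adherence means something else, the model may run but omits the dropouts: about 3 to 11 of 28 under the assumed 60% to 90% completion.

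It would go too far to say that all information on adherence is certainly lost, because neither adherence nor the second analysis set is defined. What is affected is a planned secondary analysis that the article presents as an aim and a strength. It is worth correcting because the conflict is in the text and the remedy is nearly free.

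**What to change.** In the Statistical analysis section, add one or two sentences that:
- state that the completer and per-protocol restrictions do not apply to the programme-adherence analysis;
- run that analysis on all participants given access to the programme;
- define adherence, scoring those who stop before completing session 9 as non-adherent;
- use baseline predictors only;
- report participants withdrawn under the worsening-mood rule separately, since that exit is imposed on them.

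The number of sessions completed (0 to 9) could be added as a second measure, but correcting the conflict does not require it.

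The cost is small. Baseline predictors are already collected, and no new visits or participants are needed. It is reasonable to expect that a platform which gates each session records completion, though the article does not say so. There are two limits. Predictors are restricted to baseline, because early dropouts may have no later questionnaires. Non-adherers will also be few, so the model can support very few predictors and its results should be presented as exploratory.

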## Material and methods

### Study design and participants

This study is a longitudinal randomized control-group pretest-posttest clinical trial (S1 Table). Patients with type 1 diabetes who present depression (mild to moderate) and meet the inclusion criteria will be randomized through a computer program to 2 groups. The treatment group (TG) will receive the 9-week Web-based treatment, while the control group (CG) will comprise patients on the waiting list. Evaluations in the TG will be conducted at the beginning of the program (baseline), at completion and during follow-up (3, 6, and 12 months) after treatment. For ethical reasons, the CG will receive the Web-based treatment once the TG intervention has been completed. The CG will thus be assessed at the beginning and at the end of the TG treatment. At this point, the CG will begin treatment, provided the participants still meet the eligibility criteria, and will have their corresponding evaluations. The assessments will be conducted in person.

The participants will be individuals with type 1 diabetes from the province of Malaga (Spain) who meet the following criteria:

○ Inclusion criteria: medical diagnosis of type 1 diabetes ≥ 1 year; over 18 years of age; psychological diagnosis of mild/moderate major depressive disorder, dysthymia or depressive symptomatology; no concomitant pharmacological treatment that could modify blood glucose values or depressive symptomatology; no psychological treatment at the present time; absence of the following: chronic renal failure, impaired liver function tests, active thyroid disease (except correctly substituted hypothyroidism), current pregnancy or acute ketosis decompensation at the beginning of the study; Internet access.○ Exclusion criteria: type 2 diabetes; women who are pregnant or planning to become pregnant; severe macrovascular or microvascular complications; diagnosis of major depressive disorder with risk of suicide; non-collaboration (no signed informed consent); presenting a disabling psychiatric disorder; psychosis; no Internet access.

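### The analyses are fixed on programme completers, a filter that in practice selects only the treatment group, and no all-randomised set is named

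*Protocol article*

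**What the plan says.** All points are from the protocol article.

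- **Analysis sets (Statistical analysis).** Two consecutive sentences name them: "The analyses will be carried out considering the subjects who complete the program. Analyses will also be carried out according to the protocol". Neither is ranked as primary, and neither is defined further. An intention-to-treat or all-randomised set is not mentioned in any section.
- **Design (Study design and participants).** Eligible patients "will be randomized through a computer program to 2 groups". The TG receives the nine-week programme, "while the control group (CG) will comprise patients on the waiting list".
- **Later treatment of controls (same section).** The CG is assessed at the start and at the end of the TG treatment, and only then: "At this point, the CG will begin treatment, provided the participants still meet the eligibility criteria".
- **What completion involves (Intervention).** There are nine weekly sessions with tasks: "Each session will need to be completed in order to have the following session available".
- **Drop-out (Intervention).** E-mails, calls and a mid-programme request for opinions are meant to limit drop-out, so some is anticipated. No rate is given. Participants in either group who worsen to severe depression or suicidal ideation leave the study.
- **Between-group test (Statistical analysis).** TG and CG are compared at baseline and post-treatment by t-test, Mann-Whitney test or ANOVA. Depression is the primary variable, with symptoms measured by BDI-FS.

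**The concern.** Randomisation makes the two groups comparable only if everyone randomised is kept in the group assigned. Completing nine sequential sessions happens after randomisation and is plausibly related to mood and motivation. If participants who stop are removed from one group and nobody is removed from the other on the same ground, the groups can differ at post-treatment even when the programme does nothing.

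The stake is the main result of the trial. A TG versus CG difference in BDI-FS would mix the effect of the programme with the difference between people who finish and people who do not. It would describe those who finish, not the effect of offering the programme.

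**Working it through.** **Step 1: whom the filter can remove.** Three statements, taken together, decide this.

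1. Completion is a property of the nine-session programme.
2. The CG does not have the programme until after the post-treatment assessment, and starts it only if still eligible.
3. The only TG versus CG comparison after baseline is the one at post-treatment.

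At that comparison a TG participant can be a non-completer and a CG participant cannot. With the planned 28 per group and a share q of the TG not completing, the comparison is 28(1 − q) selected participants against 28 unselected ones. For q = 20% that is about 22 against 28; for q = 40%, about 17 against 28.

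**Step 2: how large the resulting bias could be.** The plan gives no figure to reproduce here: it states neither a non-completion rate nor how completion relates to outcome. Both are assumptions below.

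Inputs:
- From Sample size calculation: 28 per group, alpha 0.05, planning effect 0.50. The two-sided test is an assumption, since sidedness is not stated. The 28 is used as stated, without judging how it was derived.
- Assumed: no true effect; CG fully observed; q from 10% to 40%; correlation ρ from 0.2 to 0.5 between the tendency to complete and a better post-treatment score.

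If the score and the completion tendency are jointly normal and the lowest share q of that tendency is removed from the TG, the spurious advantage of the TG in SD units is

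bias = ρ · φ(z_q) / (1 − q),

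where φ is the standard normal density and z_q its q-quantile.

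- q = 10%: φ(−1.282)/0.9 = 0.1755/0.9 = 0.195. With ρ = 0.2, bias = 0.039.
- q = 20%: φ(−0.842)/0.8 = 0.2800/0.8 = 0.350. With ρ = 0.3, bias = 0.105; with ρ = 0.5, 0.175.
- q = 40%: φ(−0.253)/0.6 = 0.3863/0.6 = 0.644. With ρ = 0.3, bias = 0.193; with ρ = 0.5, 0.322.

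Type I error was simulated with 28 per group, the filter on the TG only, a two-sided t-test and 20,000 runs per cell.

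| TG non-completion | ρ | Bias (SD) | Share of 0.50 | Type I error |
|---|---|---|---|---|
| 10% | 0.2 | 0.039 | 8% | 0.049 |
| 10% | 0.5 | 0.097 | 19% | 0.065 |
| 20% | 0.3 | 0.105 | 21% | 0.066 |
| 20% | 0.5 | 0.175 | 35% | 0.092 |
| 40% | 0.3 | 0.193 | 39% | 0.096 |
| 40% | 0.5 | 0.322 | 64% | 0.174 |

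A noncentral-t calculation for the last row gives 0.181, so about 0.17 to 0.18.

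**Step 3: what makes the bias vanish.** It is zero if everyone in the TG completes, or if completion is unrelated to outcome (ρ = 0). The rule that worsening participants leave the study makes at least one route to non-completion depend on the outcome itself.

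**The case against.** **An unseen analysis plan may settle it.** An article need not list every analysis set. But this article does not stay silent: it commits the analyses to completers, and a fuller plan would have to contradict it. The point rests on that statement.

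**Both sets may not be restrictive.** A reader might infer that the second set certainly drops randomised participants too. The text does not establish that. Per-protocol is the natural reading, but the word also suggests something different from completers, and analysis as allocated cannot be ruled out. This stands as an ambiguity to be cleared up. It does not alter the first set.

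**The filter might reach controls.** Controls receive the programme later, and the schedule in Fig 1 has a final point at which both groups have finished treatment and follow-up. Strictly, then, controls could be filtered on later completion. That would not restore the randomised comparison: it would select controls on continued eligibility and behaviour after the comparison is over. Their completion data may also not exist when analysis starts, since that is tied to the TG finishing.

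**The size and direction are not known.** This stands. At the low end the distortion is negligible. It could also run the other way if people stop because they have improved. The discontinuation rule covers both groups, and losing worsened controls would make the CG look better.

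**The Discussion on adherence.** A reader might take "it is known that adherence to Internet-based CBT treatment is lower than adherence when delivering the same treatment face to face" as the authors' own forecast of poor completion. It does not support that: the same sentence goes on to say that in diabetes the two ways of delivery appear not to differ, and no rate is given. The anticipation of drop-out rests on the Intervention section alone.

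**Conclusion.** The point holds. The stated completer analysis compares, at post-treatment, a selected TG with a CG that has not been selected in the same way, and the article names no all-randomised analysis beside it. That is a stated rule capable of giving a biased primary result.

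Its size cannot be derived from the documents. With no true effect and non-completion tied to worse outcome, the illustration spans 0.04 to 0.32 SD, or 8% to 64% of the planning effect, with type I error from nominal to about 0.17 to 0.18. These figures assume a fully observed CG, non-completion of 10% to 40% and correlations of 0.2 to 0.5. Bias in favour of the programme is plausible but not established, and the documents do not support saying that the result would certainly be inflated.

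**What to change.** - Name as primary the TG versus CG comparison of post-treatment BDI-FS in all randomised participants, analysed in the group assigned.
- Seek the post-treatment BDI-FS from every TG participant, whatever the number of sessions finished.
- Handle scores that are still missing with a mixed model or multiple imputation.
- Keep the completer and per-protocol analyses as supportive, and state what the phrase about analysing according to the protocol means.
- Reconcile this outcome collection with the Intervention text under which worsening participants discontinue the study, so that it is clear whether their post-treatment score is to be obtained and how they enter the analysis.

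**Cost.** Mostly wording, plus some extra follow-up. Assessments are in person, and the existing calls are there to encourage participation, so they do not by themselves deliver post-treatment scores from people who have stopped. The estimated effect may be smaller than among completers, but it would answer the question that the randomisation was set up to answer.
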